## Abstract

**Background:**

Chronic Chagas cardiomyopathy (CCC) is the most significant clinical manifestation of Chagas disease (CD) due to its impact on morbidity and mortality. Cardiac manifestations include dilated cardiomyopathy, with ventricular dysfunction, heart failure, cardiac arrhythmias and cardioembolic events. Amiodarone (AMIO) is the most commonly used antiarrhythmic drug in CCC primarily prescribed for patients with severe conduction system abnormalities. Despite preliminary evidence, no clinical study has specifically evaluated the immunomodulatory and trypanocidal effects of AMIO in patients with CCC. The main objective is to evaluate the association of AMIO therapy with serological reactivity to anti-*T. cruzi* and the inflammatory profile of patients with CCC.

**Methods/Design:**

This is a mixed (retrospective and prospective) longitudinal observational study enrolling 90 patients who will be recruited from a reference center for CD in Brazil. Patients with CCC receiving AMIO will be compared with those not receiving the drug. AMIO was prescribed at the discretion of the treating physician, independently of the present study. Eligible participants will be invited to participate during routine medical appointments. Clinical data, including electrocardiographic and echocardiographic parameters obtained during routine follow-up, will be retrospectively extracted from medical records. Blood samples will be collected at predetermined time points. The primary endpoint will be the inflammatory profile and serological reactivity to anti-*T. cruzi* in CCC patients. Secondary endpoints will include: (**1**) cardiovascular events; (**2**) CCC progression; (**3**) implantable cardioverter-defibrillator (ICD) implantation; (**4**) heart transplantation; (**5**) all-cause death and (**6**) a composite endpoint. The association between AMIO use and longitudinal changes in continuous variables will be determined using mixed linear models. Cox regression analysis will be used to investigate the relationship between AMIO use and selected outcomes (cardiovascular events, CCC progression, and death), adjusted for potential confounders. Hazard ratios (HRs) with 95% confidence intervals (CIs) will be reported.

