## Methods/Design

### Study setting

Individuals followed at the Evandro Chagas National Institute of Infectious Diseases (INI) of the Oswaldo Cruz Foundation (Fiocruz) will be invited during a medical appointment to participate in the AMIO-CHAGAS study. INI-Fiocruz, located in Rio de Janeiro, Brazil, is a national referral center for the treatment and research of infectious and tropical diseases within the framework of the Brazilian Unified Health System (SUS). INI-Fiocruz receives patients from across the country and provides comprehensive, multidisciplinary care for individuals with CD [21]. Patients currently living in the state of Rio de Janeiro with suspected or confirmed CD are referred to INI for diagnostic investigation or specialized healthcare. Many of these patients are migrants from endemic rural areas. The INI staff includes infectious disease specialists, cardiologists, gastroenterologists, nurses, nutritionists, pharmacists, and physical therapists or exercise physiologists. Patients routinely undergo blood tests, echocardiography (ECHO), electrocardiogram (ECG), 24-hour Holter monitoring, exercise testing, and cardiopulmonary exercise testing, all of which are available at this center. Data from medical records will be collected using standardized protocols. In the event of inconsistencies, records will be reviewed independently by two examiners. Only data with confirmed consistency will be included in the analyses.

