### Study design

This is a mixed (retrospective and prospective) longitudinal observational study designed to evaluate the association between chronic use of amiodarone (AMIO) and the following:

(I)**Primary outcome:** inflammatory profile, serologic reactivity to anti-*T. cruzi* antibody, and parasitic load;(II)**Secondary outcomes:** cardiovascular events (new sustained atrial arrhythmias, new sustained or non-sustained ventricular tachyarrhythmias, stroke, heart failure, atrioventricular block, and cardiovascular hospital admissions), CCC progression, internal cardioverter-defibrillator (ICD) implantation, heart transplantation, all-cause death, and a composite endpoint (including the aforementioned cardiovascular events, disease progression, ICD implantation, heart transplantation, and death).

Patients with CCC who take AMIO (exposed group) will be compared with those who do not take this drug (non-exposed group). To minimize potential confounding, patients will be matched based on the stage of CCC according to the Brazilian Consensus on Chagas Disease (A and B1 *versus* B2 and C), age (<50 years *versus* >50 years), and sex (female *versus* male) [15].

Clinical and laboratory data including blood tests, ECG, transthoracic two-dimensional echocardiography (ECHO), and 24-hour Holter monitoring, will be evaluated at three different time points:

(i)**Retrospective data**: from up to 3 years before the start of the study;(ii)**Baseline/recruitment**: at the time of inclusion in the study;(iii)**Prospective data**: during the 2 years of follow-up after recruitment;

The duration of the study, totaling five years of clinical follow-up, was established considering the CCC progresses at a rate of approximately 2% per year [22]. At recruitment, blood samples will be collected for biochemical and molecular analyses to obtain information related to the study’s primary outcome (Table 1) (Fig 1).

**Table 1 pone.0347305.t001:** AMIO-CHAGAS’s study Chronogram: Enrollment, Interventions and Outcome Assessments.

			Retrospective data	Recruitment	Prospective data
			2020 −2022	2023 - 2025	2025 - 2027
**Primary outcome:**	**Immunomodulatory effect**	Gene expression of CCC progression biomarkers in PBMCs	**–**	**x**	**–**
		Determination of serum levels of cytokines and nitric oxide	**–**	**x**	**–**
	**Trypanocidal effect**	Determination of anti-*T. cruzi* antibody titers	**–**	**x**	**–**
		*T. cruzi*-antigen quantification	**–**	**x**	**–**

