**Secondary outcomes**:	Cardiovascular events	New sustained atrial arrhythmias and new sustained or non-sustained ventricular tachyarrhythmias, stroke, heart failure, atrioventricular block and cardiovascular hospital admissions	**x**	**–**	**x**
	Disease progression	Monitored by echocardiography (ECHO), electrocardiogram (ECG), 24-hour Holter	**x**	**x**	**x**
	ICD implantation	According to the medical prescription	**–**	**–**	**x**
	Heart transplantation	According to the medical prescription	**–**	**–**	**x**
	Death of all-cause	–	**–**	**–**	**x**
	Composite endpoint	–	**–**	**–**	**x**

CCC: Chronic Chagas cardiomyopathy; ECG: Electrocardiogram; ECHO: Echocardiography; ICD: Implantable cardioverter-defibrillator; PBMCs: Peripheral blood mononuclear cells.

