### Electrocardiogram, two-dimensional transthoracic echocardiogram, 24-hour Holter and blood pressure

All analyses will be performed annually by Lapclin-Chagas (INI), by qualified professionals. The 12-lead electrocardiogram will be conducted with patients at rest, using a long recording on D2 to assess arrhythmias. The presence or absence of electrocardiographic changes will be determined according to the criteria recommended by the II Brazilian Consensus on Chagas Disease [15]. Electrocardiographic analysis will be performed using the Holter system (portable three-channel recorder and analyzer; Cardio Light® and CardioSmart® 5.0, Cardio System, São Paulo, Brazil), with three channels connected continuously for 24 hours at a rate of 200 samples per second, to detect arrhythmias predictive of mortality and to obtain the arrhythmogenic profile [29,30]. Two-dimensional transthoracic echocardiography will be performed using a phased-array ultrasound system (Philips CVx, USA) equipped with an M4S transducer, following the recommendations of the World Heart Federation [31]. Left ventricular systolic ejection fraction (LVEF), as well as left ventricular diastolic and systolic volumes, will be quantified using Simpson’s biplane method of discs. Assessments will also include left ventricular diastolic function, right ventricular (RV) systolic function, and strain parameters of the left atrium (LA), RV, and left ventricle (LV), to provide a comprehensive evaluation of cardiac mechanics. All measurements will be performed by experienced cardiologists blinded to the clinical data to minimize bias. Blood pressure will be measured on the left arm with participants seated in a quiet room after 5 minutes of rest, using an Omron digital sphygmomanometer.

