### Statistical analysis

Descriptive statistics were used to summarize the characteristics of the study population. Continuous variables will be presented as medians and interquartile ranges (IQR), and categorical variables as absolute and relative frequencies. Missing data will be assessed for their pattern and mechanism (i.e., missing completely at random (MCAR), missing at random (MAR), or missing not at random (MNAR)). The primary approach to handling missing data will be determined once the dataset is available. Depending on the extent and nature of missingness, appropriate strategies may include multiple imputation, complete case analysis, or sensitivity analyses to evaluate the robustness of the findings. The Shapiro-Wilk test will be used to assess the normality of continuous variables. When distributions deviate from normality, appropriate transformations or non-parametric tests will be applied.

Comparisons of patient characteristics according to AMIO use will be evaluated using the independent Student’s t-test for normally distributed continuous variables or the Mann-Whitney U-test for non-normally distributed data. Categorical variables will be compared using the chi-square test or Fisher’s exact test, as appropriate. Correlations between continuous variables related to the primary outcome will be assessed using Pearson or Spearman correlation coefficients, depending on data distribution. AMIO use and longitudinal changes in continuous variables will be analyzed using mixed linear models, adjusted for the duration of amiodarone use. Analyses of time course outcomes (e.g., cardiovascular events, disease progression, all-cause mortality) will be conducted using Cox proportional hazards regression models adjusted for potential confounders such as age, sex, comorbidities and previous etiologic treatment. Hazard ratios (HRs) and their 95% confidence intervals (CI) will be reported. A two-sided p-value ≤ 0.05 will be considered statistically significant.

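### Test-detected events and CCC progression are drawn from routine-care records and from annual testing, and the analysis does not account for how often each patient was tested

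*Protocol article*

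**What the plan says.** Three parts of the protocol article fix where the event and progression data come from.

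- **Source.** The Abstract (Methods/Design) says that clinical data, including ECG and echo, were "obtained during routine follow-up, will be retrospectively extracted from medical records". Study setting adds that at this centre "Patients routinely undergo blood tests, echocardiography (ECHO), electrocardiogram (ECG), 24-hour Holter monitoring", without a frequency.
- **Period.** Study design sets a look-back "from up to 3 years before the start of the study" and a prospective part "during the 2 years of follow-up after recruitment", and counts them together: "The duration of the study, totaling five years of clinical follow-up".
- **Schedule.** The section on ECG, echo, Holter and blood pressure says "All analyses will be performed annually by Lapclin-Chagas (INI), by qualified professionals". This is the only test schedule in the article.

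Table 1 marks cardiovascular events for the retrospective and prospective columns, and disease progression for all three columns. The event definition is "New sustained atrial arrhythmias and new sustained or non-sustained ventricular tachyarrhythmias, stroke, heart failure, atrioventricular block and cardiovascular hospital admissions". Progression is followed by echo, ECG and Holter. ICD implantation, heart transplantation, death and the composite are marked prospective only.

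Statistical analysis specifies Cox models for events, progression and mortality. Age, sex, comorbidities and previous etiologic treatment are given as examples of confounders. For continuous variables, "AMIO use and longitudinal changes in continuous variables will be analyzed using mixed linear models, adjusted for the duration of amiodarone use". Neither model names a term for era or for number of tests.

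Study population says that amiodarone was prescribed at medical discretion for atrial or ventricular arrhythmias.

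**The concern.** The event list mixes two kinds of outcome. Stroke, admission and sustained arrhythmia usually bring the patient to medical attention. Non-sustained ventricular tachyarrhythmia, AV block and ECG/echo progression are mostly found because someone ordered a test. For the second kind, the observed rate is the true rate multiplied by the chance of being tested.

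The retrospective tests were ordered in routine care. A protocol approved in September 2022 (Ethical aspects) could not have scheduled tests in 2020 to 2022, the retrospective period in Table 1. Because the exposed group is defined by a drug given for arrhythmia, closer rhythm surveillance of that group is credible. Matching on CCC stage, age and sex does not remove it. Standardised record extraction and blinded reading govern how a test is recorded or read, not whether it was done.

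At stake is the reading of the Cox results for two secondary outcomes. A difference in testing could be reported as an excess of arrhythmia or progression in amiodarone users, or could hide a benefit.

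**Working it through.** **The plan's own figures.** Follow-up is 3 + 2 = 5 years, of which up to 3 are retrospective. Study design justifies this length by progression of about 2% per year. In 90 patients that is 90 × 0.02 × 5 = 9 expected progressions over five years, and 90 × 0.02 × 2 = 3.6 over the prospective years alone.

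**Assumptions.** The article gives neither a routine test frequency nor an incidence of test-detected events. The following are assumed for illustration: a true incidence of 10% per year, equal in both groups (true HR 1); a yearly probability p of being tested in the 3 retrospective years; every patient tested yearly in the 2 prospective years; and an event seen only if a test is done in that year.

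**Step 1: a testing change shared by both groups.** The detected rate is 0.10 × p before recruitment and 0.10 after it. For p = 0.3, 0.5, 0.7 and 1.0, the after/before ratio is 1/p = 3.3, 2.0, 1.4 and 1.0. The crude rate moves, but the group comparison does not. Simulated Cox HRs on a common time origin are 1.01 (p = 0.5 in both groups) and 0.99 (p = 0.3 in both groups).

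**Step 2: testing that differs by group.** The simulated Cox HRs can be checked by hand. In each retrospective year the detected HR is p(AMIO)/p(non-AMIO), and in each prospective year it is 1. The five-year HR is close to exp[s × ln(p ratio)], where s is the share of detected events that fall in the retrospective years. Detected proportions per group are 1 − (1 − 0.1p)³ before recruitment, and the remainder × (1 − 0.9²) = remainder × 0.19 after it.

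| p, AMIO vs non-AMIO | Detected before | Detected after | s | Hand check of HR | Simulated HR |
|---|---|---|---|---|---|
| 0.9 vs 0.7 | 0.246, 0.196 | 0.143, 0.153 | 0.60 | exp(0.60 × 0.251) = 1.16 | 1.17 |
| 0.9 vs 0.5 | 0.246, 0.143 | 0.143, 0.163 | 0.56 | exp(0.56 × 0.588) = 1.39 | 1.38 |
| 0.8 vs 0.4 | 0.221, 0.115 | 0.148, 0.168 | 0.52 | exp(0.52 × 0.693) = 1.43 | 1.43 |

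**Step 3: risk ratio over the whole five years.** Suppose an arrhythmia shows on any one Holter with probability q, independently between Holters. Then k Holters find it with probability 1 − (1 − q)^k. Three retrospective Holters in users against one in non-users, plus two prospective ones in everybody, gives 5 against 3.

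- q = 0.1: 0.410/0.271 = 1.51
- q = 0.2: 0.672/0.488 = 1.38
- q = 0.3: 0.832/0.657 = 1.27

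**Limits.** Both illustrations suit transient findings such as non-sustained tachyarrhythmia. A lasting change that is missed once would usually be found at the next test, so for progression or fixed AV block the distortion would lie more in timing than in the five-year count, and would be smaller. Neither calculation applies to the mixed models: more measurements of LVEF or QTc do not by themselves shift a mean.

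**The case against.** The strongest reply is that the article never says testing was sparser before recruitment. The sentence on routine follow-up is not confined to the earlier years, the annual-testing sentence is not confined to the later ones, and Study setting describes ECG, echo and Holter as routine at this centre. A reader might infer that detection must rise at recruitment, or that most of the follow-up was known to be sparsely tested. The text supports neither. If routine testing was already annual for everyone, the problem vanishes.

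A second reply is that a change of testing shared by both groups is absorbed by the Cox baseline hazard. That stands, provided that patients share an aligned time origin. Bias in the amiodarone comparison needs testing that differs by group, or unequal look-back. The indication makes differential testing plausible but does not demonstrate it.

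A reader might also compare three Holters with one in the retrospective years alone, which gives ratios of 2.2 to 2.7 for q from 0.3 to 0.1. That leaves out the two prospective years that the same analysis includes. Over five years the same scenario gives 1.27 to 1.51.

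Finally, the Cox covariates follow the words *such as*, a single pooled model is implied by the five-year count and Table 1 rather than stated, and a separate analysis plan may add terms. This limits how far the silence on testing can be held against the article. It does not remove the design choice in Table 1 to take events that depend on testing from both eras and to group them with events that do not.

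**Conclusion.** The point holds as a conditional one. The article draws test-detected outcomes from routine-care records and from annually tested follow-up, and its analysis section does not account for testing frequency. If amiodarone users were tested more often before recruitment, a true HR of 1 would appear as about 1.2 to 1.4, and the five-year risk ratio as about 1.3 to 1.5, under the assumed testing frequencies and incidence. The direction would reverse if non-users were tested more.

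The reach is limited to non-sustained ventricular tachyarrhythmia, AV block and ECG/echo progression within two secondary outcomes. Stroke and admissions depend little on scheduled tests. ICD implantation, transplantation, death and the composite are prospective only in Table 1, so the retrospective era does not affect them. The primary biomarkers are measured at recruitment and are untouched.

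It is also tempting to conclude that the main comparison should rest on prospective tests alone. The article's own progression rate argues against that, since expected progressions would fall from about 9 to about 3.6. An era-by-amiodarone interaction could not be estimated usefully on so few events, and keeping only patient-years in which tests were done would select on the process suspected of differing by exposure.

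**What to change.** Keep the five-year analysis and add three items to Statistical analysis:

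1. Analyse test-detected outcomes (non-sustained ventricular tachyarrhythmia, AV block, ECG/echo progression) separately from clinically presenting events (stroke, admission, sustained arrhythmia).
2. Report the number of ECG, Holter and echo tests per patient-year, by amiodarone group and by era (before and after recruitment).
3. Add a sensitivity analysis of the test-detected outcomes limited to the scheduled prospective tests. State that any amiodarone association in these outcomes will be interpreted in light of items 2 and 3.

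The cost is a little more analysis work and a count of tests from the medical records; no new procedure is needed. The downside is low precision in the prospective-only analysis, with about 3.6 expected progressions, so it can show whether the estimate changes direction or size but cannot settle the question alone. If item 2 shows similar testing in both groups, the concern is largely answered.

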**Discussion:**

Given the limited literature on the potential trypanocidal and immunomodulatory effects of AMIO in CCC, the findings of this study may provide new insights into the therapeutic potential of AMIO beyond its established antiarrhythmic properties.

## Background

Chagas disease (CD) is an anthropozoonosis caused by the parasite *Trypanosoma cruzi* (*T. cruzi*), affecting approximately 8 million people worldwide and resulting in over 14,000 deaths annually. About 70 million people globally live in areas at risk of *T. cruzi* infection [1–4]. Cardiac chronic CD is responsible for the most significant morbidity and mortality among parasitic diseases and imposes the highest economic and health burden from parasitic diseases in the Western Hemisphere [5,6], leading to a substantial financial burden on health-care systems, with estimated health-care costs of US$690 million [7–9].

In recent decades, CD has become a global health problem due to increased migration from endemic to non-endemic areas such as Canada, the USA, Europe, Australia, and Japan. In these regions, *T. cruzi* transmission occurs mainly through vertical transmission from mother to child [1,9–11]. It is estimated that 2.8% of Latin American immigrants living in Europe are infected with *T. cruzi*, and 90% of these individuals remain undiagnosed [11].

In chronic Chagas cardiomyopathy (CCC), the replacement of cardiac fibers with connective tissue leads to loss of contractile capacity and ventricular remodeling, resulting in dilation of the cardiac chambers. These morphophysiological changes cause a gradual loss of ejection capacity, contributing to heart failure (HF) [6]. In addition to HF, arrhythmia is another important manifestation in CD patients with cardiac involvement, causing palpitations, dizziness, dyspnea, lipothymia, syncope and sudden death [12]. Arrhythmias and conduction disorders can occur in both the acute and chronic phases [13]. However, these manifestations are more frequent during the chronic phase and at any stage of the disease [14].

Amiodarone (AMIO) is the most commonly used antiarrhythmic drug in CCC primarily prescribed for abnormalities in the cardiac conduction system [12], and is considered effective in reducing both atrial and ventricular arrhythmias [15,16]. This drug is a class III antiarrhythmic according to the Vaughan Williams classification, and its mechanisms of action include inhibition of potassium, calcium, and sodium channels, thereby prolonging the plateau of the cardiac cell action potential [17,18]. Due to the scarcity of studies involving individuals with CD, the use of AMIO in patients with CCC is based on an expected benefit that should outweigh its adverse effects, such as pulmonary toxicity, polyneuropathy, gastrointestinal discomfort, bradycardia, hepatotoxicity, thyroid dysfunction, and ocular complications [15,19,20]. Therefore, this study will evaluate the potential benefits associated with the use of AMIO in patients with CCC, including possible trypanocidal and immunomodulatory effects of this antiarrhythmic drug.

